#### Sensitivity Analyses

Planned sensitivity analyses will include (1) calculating parametric and asymptotic *P* values and CIs, (2) generalized additive models to examine whether results differ when allowing nonlinear associations between baseline and postintervention symptoms, (3) per-protocol analyses based only on participants who completed all core intervention components, and (4) assessing group differences in intervention duration and the impact of intervention completion time on outcomes.

### Ethics Approval and Adverse Events

This study received ethics approval from the Human Research Ethics Committee at Monash University (ethics ID number: 25825). Any protocol modifications will be communicated to the Human Research Ethics Committee and participants. The primary investigator will make safety and progress reports to the ethics committee at least annually and within 3 months of study completion. Adverse events will be tracked in the following ways: (1) a >10-point worsening (at any time point compared with the previous time points) in PROMIS T scores on the anxiety or depressive symptom outcomes; (2) two questions administered at both T_2_ and T_4_ to assess the side effects due to the intervention and negative experiences, such as inappropriateness or unhelpfulness of the intervention; and (3) monitoring for any unsolicited reports of adverse events or serious adverse events (eg, mental health–related hospital admissions). In the consent form, participants are informed that the survey questions, including PROMIS anxiety and depressive symptom surveys, ask sensitive information and may be confronting, triggering temporary elevations in distress for some individuals. If this occurs, all participants are provided with relevant mental health support numbers to contact, and they could report this to the researchers.

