### Interventions

Both the CM and CL intervention conditions are internet-delivered programs comprising 4 modules (2 weeks of content per module), which may take participants as few as 8 weeks to complete. Both interventions comprise educational readings and videos followed by activities on the web. The activities include textboxes for participants to provide written responses to encourage active reflections. All intervention materials and activities are delivered on the web via REDCap. Multimedia Appendix 1 illustrates examples of visual snapshots of activities in each intervention. All web-based activity responses completed by the participants are available for researchers to view, allowing intervention adherence to be assessed. At the beginning of each intervention and to enhance motivation, all participants are encouraged to set treatment goals. To improve engagement and provide additional support, all participants are offered an optional midintervention phone call (approximately 15 minutes) between modules 2 and 3. Upon completion of T_5_, all participants receive the alternative group’s intervention material via an email link (ie, combined psychoeducational readings and video links).

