#### Treatment Group: CM

CM is a web-based version of the UP’s Transdiagnostic Treatment for Emotional Disorders [15]. The overall goal of the UP is to help individuals understand and recognize their emotions and respond to uncomfortable emotions in a more adaptive manner. Participants allocated to CM receive four UP-adapted modules titled (1) understanding emotions, (2) mindful emotion awareness, (3) flexible thinking, and (4) doing things differently. CM is a reduced format of the UP, as 2 core UP modules (modules 6 and 7) have been excluded from CM owing to their sole focus on exposure therapy, which was deemed inappropriate for remote delivery for individuals experiencing chronic health conditions. In CM, each module comprises 14 daily activities on the web (3-10 minutes each), which allow participants to apply what they have learned from the psychoeducational readings and videos. Participants are not expected to complete *every* daily activity, although they must complete at least 1 to 2 core activities per module before they could move on to the subsequent module. This format aims to mirror a more real-life, clinician-led intervention, where clients would not prematurely progress to a subsequent and more advanced module without first being exposed to fundamental skills from the previous modules (ie, in CM, participants must first learn about what an emotion is [module 1] before they can begin to mindfully engage with their emotional experiences [module 2] and change them [modules 3 and 4]). As a result, participants who reach the end of the entire intervention have been exposed to all core skills. Each module is outlined in subsequent sections, and a summary overview is provided in Table 1.

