#### Control Group: CL

In parallel to the CM modules, the CL group receives four internet-delivered modules that focus on different lifestyle domains: (1) diet, (2) physical activity, (3) relaxation, and (4) sleep. Throughout each 2-week module, participants are sent 2 activity links via email, whereby they are asked to apply what they have learned from the module (eg, *describe how you applied the module material to your life*
*over the past week* and *describe how you plan to apply the module material to your life over the next week*). Participants may take 3 to 10 minutes to complete each reflective activity on the web. Although the CL participants are sent fewer application activities on the web than the CM participants, they are still encouraged to apply the module material to their daily lives over the 2-week module duration. The content included in CL is publicly available, except for sleep hygiene information, which was developed by the Monash University sleep research group. The content of each module is outlined in the subsequent sections.

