**Other measures**																		
		Depression Risk Questionnaire-7	7		✓		N/A		N/A		N/A		N/A		N/A			
		Positive Affect Subscale	10		✓		N/A		N/A		N/A		✓		✓			
		Demographic and cancer information	39		✓		N/A		N/A		N/A		N/A		N/A			
		Health service use (eg, current medications, mental health treatment)	10		✓		N/A		N/A		N/A		✓		✓			
		Program evaluation (Client Satisfaction Questionnaire and open feedback)	10		N/A		N/A		N/A		N/A		✓		N/A			
		Credibility Expectancy Questionnaire	6		✓		N/A		N/A		N/A		N/A		N/A			
		Adverse events (assessed throughout)	N/A		N/A		✓		✓		✓		✓		✓			
		COVID-19 pandemic impact and distress	2		✓		N/A		N/A		N/A		✓		N/A			
		MINI^n^	5 mins		✓		N/A		N/A		N/A		N/A		N/A			

^a^Completion times: T0, T4, and T5 were 25 minutes each; T1-T3 were 10 minutes each.

^b^CM: CanCope Mind.

^c^N/A: not applicable.

^d^Measure administered at that time point.

^e^CL: CanCope Lifestyle.

^f^DERS-SF: Difficulties With Emotion Regulation Scale–Short Form.

^g^PROMIS: Patient-Reported Outcomes Measurement Information System. The PROMIS scales are all computer-adaptive tests, which means that they vary in the number of items administered depending on the participants’ prior responses.

^h^QoL: quality of life.

^i^BES: Beliefs About Emotions Scale.

^j^SMQ: Southampton Mindfulness Questionnaire.

^k^CERQ: Cognitive Emotional Regulation Questionnaire. “Catastrophizing” and “Refocus on Planning” subscales.

^l^UP-CSQ: Unified Protocol–Cognitive Skills Questionnaire.

^m^MEAQ-30: Multidimensional Experiential Avoidance Questionnaire-30.

^n^MINI: Mini International Neuropsychiatric Interview.

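### Serious adverse events are sought only through unsolicited reports, and the health service use answers collected at T0, T4 and T5 are not listed as a safety source

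*Protocol article*

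**What the plan says.** The section Ethics Approval and Adverse Events of the protocol article sets out three ways of tracking adverse events:

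1. "a >10-point worsening (at any time point compared with the previous time points) in PROMIS T scores", applied to the anxiety and depression scales;
2. "two questions administered at both T_2_ and T_4_ to assess the side effects due to the intervention and negative experiences";
3. "monitoring for any unsolicited reports of adverse events or serious adverse events (eg, mental health–related hospital admissions".

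Table 3, under Other measures, has a row "Adverse events (assessed throughout" that carries no item count and is ticked at T1, T2, T3, T4 and T5. The same block contains a 10-item measure, "Health service use (eg, current medications, mental health treatment", ticked at T0, T4 and T5. Both arms follow this schedule. The adverse-event section does not mention the health service measure.

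**The concern.** Serious events, and the mental health admissions given as their example, appear only under the third route, so they depend on a participant or someone else coming forward. The second route is solicited, but it asks about effects attributed to the intervention and about the intervention being unsuitable or unhelpful. As described, it does not ask about admissions or new treatment. The first route sees an event only through its trace in a symptom score.

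Meanwhile the trial puts questions on mental health treatment and medication to participants in both arms, at baseline and twice afterwards, and does not connect the answers to safety. At stake is the meaning of the final safety statement and of the reports promised to the ethics committee. With no solicited route aimed at serious events, a count of zero says little more than that nobody volunteered one.

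**Working it through.** The plan states no safety figure to reproduce. The check sets the sources side by side and then works out how far the unused one reaches.

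**Step 1. What each source can show.**

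| Source | When | Listed as an adverse-event route? | Bearing on a serious event |
|---|---|---|---|
| PROMIS anxiety or depression worsening | T1 to T5, against earlier time points | Yes | Indirect, through symptoms |
| Two questions | T2 and T4 | Yes | Side effects of the intervention and negative experiences; admissions not mentioned |
| Unsolicited reports | Any time | Yes | The only route naming serious events and admissions |
| Health service use survey | T0, T4, T5 | No | Current medication and mental health treatment |

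**Step 2. The follow-up period.** T5 comes 3 months after T4. The two questions are not stated for T5. The PROMIS scales look back 7 days (Secondary Outcomes). A crisis that arose and settled more than a week before T5 need not move the T5 score, so in that interval an admission could be recorded only if volunteered. The T5 health service answers are the one other scheduled source that could point to it.

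**Step 3. Whether a change from T0 can be read.** The exclusion criteria remove people in regular sessions with a psychologist or counselor, and people who changed psychotropic medication in the previous 2 weeks or planned to do so during the 8-week trial. Stable medication is allowed. New treatment or a new psychotropic at T4 is therefore a departure from the entry state, provided that each person's answer is compared with their own T0 answer. At T5 the reading is weaker, because the criteria on planned treatment cover only the 8 weeks.

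**Step 4. Text against Table 3.** The text places the solicited questions at T2 and T4; the table ticks adverse events at T1 to T5. The two can be squared if the ticks stand for the PROMIS rule and unsolicited reports. The table does not say so, and a reader could take it to mean that adverse events are asked about at every survey.

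**Step 5. Reach of the survey at T4.** Inputs from the Results section: randomized CM 110, CL 114, total 224; finished with T4 surveys CM 61, CL 75.

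- CM: 61/110 = 55.5% reached; 49/110 = 44.5% not reached.
- CL: 75/114 = 65.8% reached; 39/114 = 34.2% not reached.
- Overall: (61 + 75)/224 = 136/224 = 60.7% reached; 88/224 = 39.3% not reached.
- Difference between arms: 65.8 − 55.5 = 10.3 percentage points.

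The number responding at T5 is not given.

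**The case against.** The strongest reply is that solicited capture already exists. PROMIS scores are taken at every time point in both arms with a defined worsening rule, and two direct questions are asked twice. That stands: it would be wrong to say that adverse events in general rest on volunteered reports, or that treatment data are more direct evidence of deterioration than repeated symptom scores. It does not supply a solicited route for serious events.

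A second reply is that a journal article condenses, and the full protocol may already send these answers to safety review. That is possible. But the article does not merely stay silent: it gives a closed list of three routes, and this source is not among them.

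A third reply is that the remedy is incomplete. This stands too. The survey's named examples do not include admissions. Participants who miss a postmodule survey by 2 weeks are withdrawn, so someone who left because of a serious event may never be asked. The survey is on everyone's schedule, but it did not reach everyone randomized.

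A reader might go further and infer that events come to light more readily in CM, since "each module comprises 14 daily activities on the web (3-10 minutes each" there, while in CL "Throughout each 2-week module, participants are sent 2 activity links via email". The documents do not support this. Although "All web-based activity responses completed by the participants are available for researchers to view", the stated purpose is to assess adherence, and activity text is not a listed safety route. CM participants need not do every activity: Table 1 marks 2 + 2 + 1 + 2 = 7 core activities as mandatory, against 2 × 4 = 8 links sent in CL. The initial call, the optional mid-intervention call and the survey schedule are the same in both arms. No reporting probabilities are given, and lower T4 completion in CM could pull the other way, so neither the size nor the direction of any difference can be derived.

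**Conclusion.** The point holds as an inexpensive improvement to safety ascertainment. Serious events have no solicited route, T5 has no stated solicited question, and a relevant survey already scheduled in both arms is absent from the list. Its size cannot be put as a number of missed events, because the documents give neither event rates nor reporting rates. What can be stated is the ceiling on the gain at T4: 136 of 224 randomized participants, taking the reported completers as final.

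The survey supplements capture and does not complete it. Nor does it give an unbiased comparison between arms, because it shares the schedule but not the response: the 10.3-point gap in T4 completion carries straight into any by-arm count. The conclusion assumes that the article's list of three routes is the operative one.

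**What to change.** - Add the T4 and T5 health service use answers, each compared with the participant's own T0 answer, as a further solicited source in the adverse-event section.
- List by arm any new mental health treatment or new psychotropic medication since T0, separately from unsolicited reports. Show the number responding in each arm at each time point alongside.
- Label these entries as possible events for review, since new treatment may be help-seeking rather than harm. State that the survey does not name admissions and misses those withdrawn.
- Reconcile the text with the adverse-event row of Table 3: say which source each tick from T1 to T5 stands for, and whether any solicited question is asked at T1, T3 and T5.

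The cost is a sentence or two, one table and the time to review the entries. The Results section says follow-up data were collected in April 2022, so no new data and no further participant burden are involved.

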## Results

Recruitment for this trial began in September 2020 and all follow-up data were collected in April 2022. A total of 224 patients were randomized to the CM (n*=*110, 49.1%) and CL (n=114, 50.9%) groups. In total, 61 CM participants and 75 CL participants have completed the intervention and postintervention assessment surveys.

## Discussion

This manuscript outlines the protocol for a novel randomized controlled trial evaluating the efficacy of a multicomponent, emotion-focused, internet-delivered intervention (CM) compared with an active comparator intervention (CL) in improving emotion regulation, symptoms of anxiety and depression, and QoL in cancer survivors. The findings from this trial will extend previous pilot results, which suggested that each CM module may be independently effective in improving cancer survivors’ mental health and emotion regulation [18].

### Limitations

The results of this trial will be interpreted in the context of its limitations. For instance, as the treatment group’s effects will not be compared against the absence of any intervention (eg, wait-list control), we will not be able to assess whether improvements in either group are due to the actual interventions or a result of naturalistic tendencies (eg, natural improvement in mental health symptoms over time). In addition, the intervention intensity and thus the potential duration of CM and CL differ. Unlike in CL, CM includes mandatory core activities in each module, which must be completed before participants can progress to the subsequent modules. This means that CM participants are likely to take longer to complete the intervention, which could impact the outcomes and attrition rates. Finally, CM and CL are English language–based interventions, and the trial excludes those who cannot read or write in English, which may limit the generalizability of findings to English-speaking populations only.

### Strengths and Significance

Despite these limitations, this is the first randomized controlled trial to evaluate an emotion-focused, UP-adapted, and internet-delivered intervention designed for cancer survivors to improve their mental health and QoL. Considering (1) that most of those diagnosed with cancer survive their diagnosis [68], (2) that cancer survivors experience elevated symptoms of psychological distress and lower QoL [1,36], and (3) that cancer survivors may face economic and geographic barriers to accessing mental health support [21,23,69], the development of web-based and affordable interventions that are highly accessible is paramount. Finally, as CM is internet-guided, it is also expected to have a low therapist burden and is considered highly scalable.

Another strength of this study relates to its unique study design. The trial will allow not only an assessment of symptom improvement but also an evaluation of factors that account for symptom changes. Specifically, by concurrently measuring emotion regulation and psychopathological symptoms at all time points, the design will enable the assessment of more nuanced relationship patterns between these closely linked variables. Thus far, few studies assessing applications of the UP have been able to clearly decipher whether improvements in emotion dysregulation are truly mediating symptom improvements.

Furthermore, the study will allow a detailed assessment and comparison of each module’s effects in the treatment versus control conditions. This mechanistic analysis allows for greater treatment optimization. For example, if the target outcome of one module is found to contribute minimally compared with the other modules, then theoretically, the less effective module may be removed or decreased in intensity to reduce intervention duration and improve treatment efficiency.

In addition, the CL intervention material may prove to be a rather formidable control comparator. This is because lifestyle factors, such as diet [70], exercise [71], relaxation [72], and sleep [73], are highly correlated with mental health outcomes. Therefore, if CM is more efficacious than CL in improving emotion regulation and anxiety and depressive symptoms, such findings will speak to the strength and magnitude of the effects of CM.

## Appendix

Multimedia Appendix 1 Supplementary materials including visual snapshots of intervention activities.

## Abbreviations

CL: CanCope Lifestyle
CM: CanCope Mind
DERS-SF: Difficulties With Emotion Regulation Scale–Short Form
EDB: emotion-driven behavior
MINI: Mini International Neuropsychiatric Interview
PROMIS: Patient-Reported Outcomes Measurement Information System
QoL: quality of life
REDCap: Research Electronic Data Capture
SMD: standardized mean difference
UP: Unified Protocol
